## Abstract

**Introduction:**

Early palliative care (PC) has been recommended for older adults with cancer to address their cancer and treatment related high symptom burden and unmet needs. However, it is underutilized; older adults with cancer are 60% less likely to use PC compared to their younger counterparts. One approach to reduce existing barriers and improve utilization is to assess their readiness for PC. However, there are no gold-standard tools to measure older adults with cancer PC readiness.

**Methods:**

Informed by the 8 domains of PC recommended by National Consensus Project guidelines, Readiness to Change Framework, and principles of community engaged research, we will use a mixed methods approach, to develop and validate a Palliative Care Readiness (PALCARE) Tool through the following steps: 1) Identify items using semi-structured interviews with 20 diverse (race/ethnicity, rural/urban residence, cancer types) older adults with cancer; 2) Develop draft tool via expert panel surveys followed by focus group with PC experts, and 3) Determine item clarity and wording via cognitive interviews with 20 dyads of older adults with cancer and their family caregivers.

**Discussion/Conclusion:**

The PALCARE tool will be one of the first measures of PC readiness among a diverse sample of older adults with cancer. Once validated, PALCARE can enhance clinical practice by identifying those who are/are not ready for PC, providing targeted PC that is congruent with their readiness, and educating and supporting those who report being not yet ready for PC. The ultimate goal of this study is to improve PC early access and older adults’ quality of life.

## Introduction

Cancer is the second most common cause of death in the United States (US) affecting more than 18 million individuals [1]. Cancer incidence greatly increases with age; approximately 60% of cancer diagnoses and 70% of all cancer-related deaths occur in adults aged 65 and over [2]. Older adults with cancer experience multiple physical and psychological symptoms (e.g., pain, nausea, vomiting, diarrhea, anorexia, weight loss, malnutrition, fatigue, depression, insomnia) [3–5] and high levels of unmet physical, psychological, informational, communication, and sexual health needs [6–7] which significantly affects their quality of life (QoL). Concurrently, the aging process creates bio-psycho-social changes resulting in health and support needs [8] and is associated with occurrence of multiple chronic conditions that may worsen with cancer-related toxicities [9,10].

High symptom burden, high level of unmet needs, and presence of multiple chronic conditions increase the complexity of cancer care and cancer related decision-making in older adults with cancer. Therefore, they can greatly benefit from palliative care (PC). Early PC, typically defined as integration of PC within 8–12 weeks of diagnosis [11–13] can lead to positive outcomes such as symptom relief; improved mood, QoL and survival; increased illness understanding; overall satisfaction with care and treatment outcomes; reduced depressive symptoms; lower ICU admissions and length of stay; and reduced costs of care [11–18]. Professional organizations such as the World Health Organization [19], American Society of Clinical Oncology [20], National Consensus Project’s Clinical Practice Guidelines for Quality Palliative Care [21], and National Comprehensive Cancer Network [22] have responded to the growing needs of adults with cancer and recommend integrating PC into standard oncology care to provide quality holistic care to patients with cancer and their families [23].

Despite the positive benefits, PC is often not a part of routine cancer care among older adults with cancer and is introduced late in the disease trajectory. Many adults with cancer receive PC in the last four weeks of life, when earlier intervention would have been beneficial [24]. Older adults may show different triggers for the initiation of PC than younger populations such as frailty, pre-existing functional dependence, cognitive impairment, emotional distress, and caregiver-related problems [25]. However, older adults are 60% less likely to utilize PC compared to their younger counterparts [26,27]. PC barriers include lack of knowledge and awareness of PC, negative stereotypes/stigma (e.g., associating PC with hopelessness, death, forgoing cancer therapy, and end-of-life care) [28,29], denying the terminal nature of the disease, and requesting not to be referred to PC or not showing up to PC clinics or missing PC appointments when referred [30,31]. Other characteristics associated with low PC use are being male, unmarried, a racial minority, low socio-economic status, residing in a rural area, and fee-for-service enrollees [32]. Lack of or delays in PC referral result in poor symptom management, reduced QoL, and unwanted uncomfortable end-of-life care [33].

One approach to reducing barriers and improving PC utilization among older adults with cancer is to systematically measure their readiness for PC. The concept of ‘readiness’ has been established in previous studies as integral to making and maintaining a health behavioral change including for excessive drinking [34], smoking [35], substance abuse [36], exercise [37], and adherence to treatment [38]. Evidence shows that when patients experience a high degree of readiness, they view their disease condition in a more positive light and report less anger and depression [39]. Readiness also has been studied in the context of advance care planning [40] but not in the context of PC among patients with cancer.

There is no standardized tool to measure readiness for early PC in older adults with cancer. While there are tools to decide the timing for PC referral, most tools focus on providers’ perspectives on triggers for PC referrals [41–48] and do not focus specifically on patients with cancer [40–52]. One tool [53] examines perceptions of – but not readiness for PC and is not tailored for older adults. Most tools address just one or two NCP guidelines domains [50]; none cover all eight domains of PC [41–53]. Currently, one tool “Advance Care Planning Engagement Survey” assesses readiness in advance care planning decision-making [40] but focuses on end-of-life decision-making rather than early PC. Finally, one PC instrument [53], “Perceptions of Palliative Care Instrument (PPCI)” includes one global question (domain) on readiness to hear about PC, namely “*How ready are you to hear about palliative care today?”* (Response options, 0 = not at all to 10 = totally). This question, however, targets the readiness to hear about PC -- not readiness for accepting or receiving it. It does not ask about readiness for PC in the eight specific domains of PC listed in the NCP guidelines, and it is not specifically designed for older adults with cancer [53]. There is an urgent need to develop a PC readiness tool that holistically assesses all eight NCP domains of PC and is specifically tailored to meet the needs of older adults with cancer. The proposed Palliative Care Readiness (PALCARE) tool will expand the range of PC domains by including all eight domains of PC listed in the NCP guidelines and will be guided by the Readiness to Change Framework. A tool assessing PC readiness can allow the oncology team to provide targeted PC in the domains where they feel ready, educate and suggest benefits in domains where they are not yet ready, and ultimately prepare them to accept referral to interdisciplinary PC team which may lead to patients’ improved quality of life.

## Guiding Frameworks

Our study is guided by a synthesized theoretical framework using a) National Consensus Project (NCP) for Quality Palliative Care guidelines [21] and b) Readiness to Change Framework [39].

### NCP Project Guidelines

The NCP project created clinical practice guidelines targeted towards improving PC quality and standards across all care settings [21]. The NCP guidelines describe eight domains of quality PC: 1) structure and process of care; 2) physical aspects of care; 3) psychological and psychiatric aspects of care; 4) social aspects of care; 5) spiritual, religious, and existential aspects of care; 6) cultural aspects of care; 7) end-of-life care; 8) ethical and legal aspects of care [21] which can ensure holistic and equitable quality PC to older adults with cancer.

### Readiness to Change Framework

Dalton and Gotlieb [39] developed the Readiness to Change Framework which states three phases that characterize the process of readiness prior to a behavioral change: a) realizing what needs to change, b) weighing the cost and benefit, and c) planning for action. The first phase is becoming aware of and realizing what needs to change. The second phase involves appraising the costs and benefits of the proposed change and determining whether to change or not. When an individual decides that the benefits of the proposed change are greater than the costs, the final phase of the readiness process begins. The final readiness phase involves their desire or willingness to change and planning for action towards that change [39]. Using this framework, the readiness for PC among older adults with cancer may occur in three phases: 1) realizing they have high symptom burden and other unmet needs that may benefit from PC; 2) weighing PC costs and benefits of PC; and 3) planning to receive PC.

Fig 1 illustrates the eight domains of PC recommended by the NCP guidelines that PALCARE items will cover and the three phases of readiness that will be used to construct response categories for the questions.

**Fig 1 pone.0323366.g001:**
[figure not shown]
Conceptual Framework.

### Principles of community engaged research

This research will be informed by the principles of community engaged research [54] Community engagement is a process where researchers work collaboratively with groups of people to identify and address issues that are affecting their health/well-being. The aim of community engaged research is to build trust, identify new resources, create better communication between researchers and community members, and create long-standing collaborations [54]. Community engaged research has been shown to address health disparities resulting in positive health outcomes [54–56]. Community based participatory approach (CBPR) is considered to be the gold standard to reduce disparities, create and administer culturally concordant palliative care interventions, and improve health outcomes among individuals with serious illness [56–58].

For this R15 research project, we will use the ‘continuum of community engagement in research’ framework developed/recommended by Key and colleagues [54] which can range from consultation with community partners to community driven research [54]. They have identified 7 levels of community engagement in research: 1) No community involvement 2) Community informed 3) Community Consultation 4) Community Participation 5) Community Initiated 6) Community Based Participatory Research 7) Community Driven/Community Led [54]. For this research, we will use the third level of community engagement, ‘*community consultation’* by forming a patient and family advisory board consisting of older adults with cancer and their family caregivers to seek feedback on study flyers, other recruitment materials, and semi-structured interview guide questions. Evidence shows that collaborating on interview guide with community members can allow researchers to seek feedback on question depth, appropriateness, and clarity and ensure that the questions asked are more representative of the population (especially those from underrepresented backgrounds) [59].

The PALCARE tool is proposed to be developed and validated for diverse older adults with cancer comprising Caucasian/White, African American/Black, and Hispanic race/ethnicity. Therefore, we will assemble a patient and family advisory board of approximately 6–8 members representative of the above race/ethnicities and seek feedback on study materials (*which has been formed and convened as of December 2024*)*.*

## Materials and methods

### Study design

Using a mixed methods approach, this 3- year study will iteratively develop and establish the content validity and preliminary convergent validity and test-retest reliability of the PALCARE tool for older adults with cancer through three specific aims.

#### Aim 1.

Develop the Palliative Care Readiness tool (PALCARE) for older adults with cancer. To develop the initial items pool, semi-structured interviews will be conducted with a diverse group of 20 older adults with cancer (diverse race/ethnicity, rural/urban residence, common types of cancer).

#### Aim 2.

Establish the content validity of the PALCARE tool. We will assess content validity in three steps: a) two rounds of expert panel review (via an online survey) with 10 PC experts including physicians, nurses, social workers, and chaplains; b) a focus group with 6 PC experts; c) cognitive interviews with 20 dyads of older adults with cancer and their family caregivers (40 in total) to gain additional insights on PALCARE questions.

#### Aim 3.

Establish preliminary convergent validity and test-retest reliability of the PALCARE tool: We will assess a) convergent validity of the PALCARE tool by correlating the PALCARE with the global readiness to hear about PC from the Perceptions of Palliative Care Instrument (PPCI) [53], and b) test-retest reliability by assessing readiness for PC using the PALCARE tool during the cognitive interview and 2 weeks afterward.

The three specific aims which will be conducted over 4 phases (see Table 1).

**Table 1 pone.0323366.t001:** Overview of methods/specific aim for each study phase.

Specific Aims	Study phase
1) Develop PALCARE tool	**Phase 1**: Semi-structured interviews with a diverse group of 20 older adults with cancer (White, Black, and Hispanics)
2) Establish the content validity of the PALCARE tool	**Phase 2**: Two rounds of expert panel survey with 10 PC experts; **Phase 3**: Focus group with 6 PC experts **Phase 4**: Cognitive interviews with 20 diverse group of dyads of older adults with cancer and their family caregivers
3) Establish the preliminary convergent validity and test-retest reliability of the PALCARE tool	**Phase 4**: Cognitive interviews with measurement of the global question on PC readiness from the Perceptions of Palliative Care Instrument (PPCI) and repeatedly assessing PALCARE before the cognitive interview and 2 weeks afterward.

## Phase 1: Semi-structured interviews

We will develop the initial items pool via semi-structured interviews with a diverse group of 20 older adults with cancer (diverse race/ethnicity, rural/urban residence, common types of cancer). This sample size was chosen based on previous studies who recruited 15–20 participants for initial development of PC tools [53,60]. We anticipate that 20 participants will provide data saturation, but we will continue to recruit until data saturation [61]. Semi-structured interviews will be led by the study PI at times and locations that are convenient for the participants. Institutional Review Board approval for this protocol has been obtained from the University of North Carolina at Charlotte and Atrium Health (recruitment site).

### Eligibility criteria.

Participant eligibility will include the following: a) ≥60 years, b) diagnosis of advanced cancer (metastatic, stage III or IV solid tumors), c) no current enrollment in hospice care; d) ability to communicate in English. Exclusion criteria include a) those under age 60 years, b) non-advanced cancer, c) enrolled in hospice care, d) inability to communicate in English, and e) cognitive impairment as indicated by the Callahan assessment tool [62]. We selected the age criteria of 60 years and above for recruitment because recent evidence suggests that geriatric impairments and frailty are prevalent and commonly occur in individuals as early as age 60 years [63]. Also, cancer occurs in much earlier age among patients belonging to racial/ethnic minority backgrounds [64].

### Recruitment.

Participants will be recruited from a cancer center located in North Carolina. We aim to purposively and proportionately recruit older adults with cancer from diverse racial and ethnic backgrounds (White, Black, Hispanic) from rural and urban areas and diagnosed with one of the four most common cancers in older adults (colorectal, lung and bronchus, prostate, breast). Although preferences will be given to the four most common cancers, we will include older adults with any advanced cancer. Participants will be recruited by our health systems collaborator by using electronic health records (EHR) to identify eligible study participants. To further enhance recruitment, we will also employ a multi-method approach including posted flyers, personal visits to the cancer center, and referrals from other clinicians and key stakeholders.

### Data collection.

Informed consent will be obtained from participants prior to data collection (written informed consent for in-person interviews and verbal consents for virtual participants). After completing informed consent, interested and eligible older adults with cancer will be asked to complete the demographic health form that will consist of participant’s age, sex, ethnicity, race, educational level, marital status, employment status, annual household income, health insurance, cancer type and stage, and place of residence (rural vs urban). We will use semi-structured interviews to generate initial PALCARE items. The research team has developed a semi-structured interview guide which will include real-life scenarios related to PC readiness and will identify factors related to the eight domains of PC listed in the NCP guidelines (See Table 2 for general topics for each of the 8 domains). We will begin the interview by asking participants an overarching question “Tell me about a common symptom/situation you have experienced where you needed care or support.” Directed probe questions/statements will be used to identify readiness for PC in each eight domains of PC listed in the NCP guidelines. Participants may choose to receive a $50 Amazon gift card to thank them for their time. Data collection is planned to begin from late March of 2025. We anticipate having a first draft of the PALCARE tool by December of 2025.

**Table 2 pone.0323366.t002:** Example Topics for Item Generation for all 8 Domains of PC Listed in the NCP Guidelines.

Eight Domains of PC	Example of Topics
1. Structure and process of care	Conversations with the patient, family caregivers, and clinicians; patient and family understanding of the serious illness; goals of care; treatment preferences;
2. Physical aspects of care	Pain and other physical symptoms; functional status; symptom distress; QoL.
3. Psychological and psychiatric aspects of care	Emotional distress; anxiety; depression; delirium; dementia; family dynamics; coping strategies.
4. Social aspects of care	Family structure and function; quality of relationships; communication; decision-making preferences; social support; resiliency; support system for respite; community resources;
5. Spiritual, religious, and existential aspects of care	Sources of spiritual strength and support; existential concerns such as lack of meaning; question of existence; meaning and suffering; relationship with God;
6. Cultural aspects of care	Cultural practices, beliefs, values during serious illness; dying process; time of death and post death; preferred names and pronouns; interaction with the PC team; truth telling or not sharing diagnosis; preferred taboo and practices; health literacy; acculturation.
7. Care of the patient nearing the end of life	End of life: signs and symptoms that patient is nearing death; prepare caregivers how to recognize and manage common symptoms; document patients’ wishes and preferences;
8. Ethical and legal aspects of care	Advance directives; patients’ values and preferences; spiritual beliefs are routinely reviewed and documented with attention to changes in health care status

### Data analysis.

All qualitative interview data will be audio-taped, transcribed verbatim, and checked for accuracy. Data will be analyzed using content analysis [65] aided by NVivo software. Two researchers will code each transcript. [name] will lead the analysis. Content analysis will lead to generation of a list of codes which will be reviewed for redundancy. An initial item pool will then be developed from the codes with items in each of the 8 domains listed in the NCP guidelines.

### Phase 2: Expert panel review to establish the content validity of the PALCARE tool

To establish content validity, two rounds of expert panel review will be conducted with 10 PC and geriatric oncology experts who will independently review the PALCARE tool. These diverse experts will include four physicians, two nurses, two social workers, and two chaplains. Using an iterative process, experts will independently score each PALCARE item to see if it assesses PC readiness and addresses each of the eight PC domains. This step is essential in determining whether the content is pertinent to PC theory and practice and will help refine the tool as necessary.

#### Recruitment.

Experts will be recruited from the research team’s professional networks: PC and geriatric oncology related organizations such as Hospice and Palliative Nurses Association (HPNA), International Society of Geriatric Oncology (SIOG), and Cancer and Aging Research Group (CARG), based on their clinical experiences and expertise working with older adults with cancer from diverse racial and ethnic backgrounds, types of cancer, rural/urban residence with the target population [66] (such as certification or full-time employment for at least three years in a setting caring for older adults with cancer and PC).

#### Data collection.

Each expert will be invited to participate in the expert panel review with a standardized explanation of the study. They will meet with the PI if they have questions. After they provide informed consent, we will send experts a Qualtrics online survey which will describe the goal of the tool, including the initial item pool. Experts will be asked to initially evaluate each item on a visual analogue Likert-type scale ranging from 1 to 10 (1 = extremely inadequate to 10 = extremely adequate) based on the following criteria a) relevance of each item to PC readiness, b) how well each item reflects the respective eight PC domains listed in the NCP guidelines, c) readability and appropriateness of the item for older adults with cancer. For any item the expert rate ≤ 6 (out of 10), a comment box will be provided where they can address each item’s relevance, readability, and appropriateness. Items will remain if they receive an average rating of greater than 6. Finally, panelists will be asked to recommend items that may have been missed. Based on their recommendations, items will be revised, dropped, or added. We will then send the revised item pool to the same experts for a second round of review. Each survey is expected to take approximately 30 minutes.

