#### Data analysis.

After data collection is complete, information will be cleaned and stored on the private and secure computers of the research team. Responses will be reviewed to further refine the item pool. The study team will review descriptive and qualitative feedback to identify problematic items that need revision. The content validity index (CVI) will determine the relevance of items, evidence of the validity of the content [67] and retention of items in the tool [68]. At the end of the second expert panel review, items with an CVI < 0.78 will be considered problematic and will be deleted or modified.

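### The round 1 screen (mean rating above 6) is far looser than the final CVI criterion of 0.78, which is applied only after the last rating round

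*Protocol article*

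**What the plan says.** The protocol article (Phase 2) states that "two rounds of expert panel review will be conducted with 10 PC and geriatric oncology experts who will independently review the PALCARE tool". Under Data collection, each item is scored from 1 to 10 on three criteria: relevance to readiness, fit to the palliative care domain, and readability and appropriateness. Low scores prompt comments: "For any item the expert rate ≤ 6 (out of 10), a comment box will be provided". The retention rule that goes with this initial rating is "Items will remain if they receive an average rating of greater than 6". Experts may also propose missing items. Then "Based on their recommendations, items will be revised, dropped, or added", and "We will then send the revised item pool to the same experts for a second round of review".

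Under Data analysis, the CVI is named as the measure that settles relevance and retention, with this rule: "At the end of the second expert panel review, items with an CVI < 0.78 will be considered problematic and will be deleted or modified".

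No third rating round is described. A focus group with a goal of six of the same experts follows (Phase 3), then cognitive interviews with 20 dyads (Phase 4).

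**The concern.** The two rules measure different things. The mean uses the size of every rating, so a few high scores can carry an item. The CVI counts how many experts judge the item relevant, whatever the strength of their view. A mean just above 6 on a 1 to 10 scale sits slightly over the midpoint of 5.5, whereas 0.78 asks for near-consensus.

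The order makes this matter. Round 1 is the only point at which a weak item can be reworded and rated again by the panel. The lenient rule operates there, and the demanding rule operates once no rating round is left. An item deleted at that stage causes no difficulty. An item modified at that stage can go forward with no index for the wording that is used. Aim 2 is to establish content validity, and the CVI is its quantitative evidence.

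**Working it through.** **Inputs from the article.** Ten experts, the same in both rounds; ratings from 1 to 10; mean above 6 to remain; CVI below 0.78 is problematic, judged after round 2. The article gives no figure for how many items each rule would keep, so there is none to reproduce.

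**Input assumed.** A CVI needs a cut: the lowest rating *c* that counts as relevant. The article does not give one, so 6, 7 and 8 are all tried. The value 7 mirrors the comment-box trigger of 6 or below, but the article does not present that trigger as a CVI cut.

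**Step 1: what 0.78 means.** CVI = *k*/10, where *k* is the number of experts at or above *c*. 7/10 = 0.70 fails and 8/10 = 0.80 passes, so the criterion is at least 8 of 10.

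**Step 2: how little support the mean rule needs.** With *k* experts at or above *c*, the largest possible mean is [10*k* + (10 − *k*)(*c* − 1)]/10.

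- *c* = 6: 5 + 0.5*k* > 6 needs *k* of at least 3 (CVI 0.30).
- *c* = 7: 6 + 0.4*k* > 6 needs *k* of at least 1 (CVI 0.10).
- *c* = 8: 7 + 0.3*k* > 6 holds even at *k* = 0 (CVI 0.00).

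**Step 3: examples at *c* = 7.**

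| Ratings | Mean | Mean rule | CVI | CVI rule |
|---|---|---|---|---|
| nine 6s, one 7 | (54 + 7)/10 = 6.1 | kept | 0.10 | fails |
| six 4s, four 10s | (24 + 40)/10 = 6.4 | kept | 0.40 | fails |
| six 10s, four 1s | (60 + 4)/10 = 6.4 | kept | 0.60 | fails |
| eight 7s, two 1s | (56 + 2)/10 = 5.8 | dropped | 0.80 | passes |

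**Step 4: how often the rules differ.** These examples show what is possible, not what is common. The simulation used 200,000 items with 10 raters each and normal ratings rounded and clipped to 1 to 10. The assumptions were an overall mean of 6.5 to 8, a rater SD of 1.5 to 2.5 and an item SD of 1. Both rules were applied to the same ratings.

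| Rating counted as relevant | Items kept by the mean that have CVI below 0.78 |
|---|---|
| 6 or above | about 7% to 47% |
| 7 or above | about 30% to 80% |
| 8 or above | about 65% to 95% |

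Kept items with fewer than 5 of 10 experts in favour are much rarer: about 4% to 16% at a cut of 7, and under 1% at a cut of 6. At a cut of 8 they are more common. In a simpler run with no spread between items and a rater SD of 2, the share is 60% at a true mean of 7 and 17% at a true mean of 8.

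In the main simulation, the opposite error (an item meets the CVI but is dropped by the mean) affects about 1% of items or fewer at any cut. At a cut of 8 it cannot occur, since eight 8s and two 1s already give (64 + 2)/10 = 6.6.

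**Step 5: what happens after a failure.** The initial rating leads to the mean screen, comments and revision, and then to a second rating. The second rating leads to the CVI, and then to deletion or modification. Phases 3 and 4 gather discussion, probing and problem coding for the items. Neither has the experts rate an item again, so neither yields a CVI for a modified one.

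**The case against.** The case against is substantial, and much of it stands.

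- **The rules run in sequence.** A reader might infer that they contradict each other. They do not: a permissive first screen followed by a stricter final criterion can be carried out exactly as written, and no item stays on the mean alone once the CVI is applied. The accurate description is that they are misaligned.
- **Majority-rejected items.** A reader might infer from the examples that items most experts reject will routinely survive. At cuts of 6 and 7, most of the mismatch comes from items with 5 to 7 of 10 experts in favour. Only a cut of 8 would make majority rejection common, and the article does not set one.
- **Good items lost.** The last example in the table is possible but contrived, and the simulation shows this loss to be rare. The mean rule is looser rather than wrong in both directions.
- **Pooled criteria.** A reader might infer that good readability scores mask poor relevance. That would need the three criteria to be averaged together, which the article does not say.
- **Other safeguards.** Low raters can comment, the team reviews that feedback, items can be revised or dropped between rounds, and the focus group and cognitive interviews come later. These will rescue some items, and the simulation does not model them.
- **Later edits.** Cognitive interviews may change wording too, so even items that pass may end up worded differently from what was rated. That is true, but refining the wording of an item judged relevant differs from reworking one that failed on relevance.
- **The cut.** The full protocol may define which rating counts as relevant, and an article may leave that out. Its absence is therefore not the defect here; it only widens the range of the result.

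None of this answers the remaining point: the criterion that decides retention is first consulted when no rating round is left.

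**Conclusion.** The concern holds as a misalignment of stringency and timing. The mean screen is looser than the CVI criterion at every cut tried. Depending on the cut, between about 7% and 95% of items kept on the mean would fail the CVI on the same ratings, with 30% to 80% at the cut that mirrors the comment-box trigger. These shares rest on assumed rating distributions and take no account of revision between rounds, so they measure the gap between the two rules and do not forecast how many items will fail in round 2. That an item modified after round 2 has no CVI for its final wording does not depend on the simulation. It follows from the order of steps in the article. The consequence is a gap in the evidence for Aim 2; it does not invalidate the tool.

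**What to change.** Three changes to the Phase 2 wording:

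1. State which rating on the 1 to 10 scale counts as relevant for the CVI. A rating of 7 or above is one natural choice, since it matches the existing comment trigger of 6 or below.
2. Compute the item CVI from the relevance ratings in round 1 as well as in round 2.
3. In round 1, use a CVI below 0.78 (fewer than 8 of 10 experts) to flag items for revision and re-rating in round 2, in place of relying on the mean alone.

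The survey, the panel and the number of rounds are unchanged, and the data needed are already collected. The cost is that more items will be flagged after round 1, so there is more revision work between rounds. Some items may still fail for the first time in round 2. If such an item is modified and kept, the report should say that its final wording was not rated.
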